#### STUDY II

A subset of Study I participants will be asked to participate in this related study with more rigorous and intensive assessments. Students attending two or three selected classrooms within each school will be invited to participate in Study II. To be eligible, students must be (a) enrolled into Study I, and (b) own a smartphone. In addition to completing the baseline questionnaire, participants in Study II are being asked to wear a wrist-based accelerometer and to complete EMA prompts via their smartphone five times a day over a seven-day study period. In an attempt to capture the most representative sample at baseline, two to three English classes will be randomly selected from each school (all students are required to take English in their grade 11 year). Specifically, one university, college, and vocational stream class will be selected at each school in an attempt to capture different post-high school trajectories (i.e., entering postsecondary education, joining the workforce, etc.).

A research assistant will attend these select classes, providing all students with the purpose and study requirements of Study II. Pre-populated study packages including an accelerometer and a personalized code for an EMA app will be distributed to students interested in participating. Participants will be then be asked to download an EMA app developed for this study called Lumedi (designed and developed by Webility Solutions Inc.), and to enter the unique code provided. Immediately following this, they will be instructed to put the accelerometer on their non-dominant hand and to wear it for as much as they can over the next week (with the exception of showering and participation in water-based activities), and to answer as many of the five prompts on each day. Given the high participant burden, participants will be provided with $100 gift card for participation at baseline and each subsequent follow-up period.

### Measurements

#### Socio-demographic factors

Participants will be asked to respond to demographic questions that include items to self-report age, grade, gender, ethnicity, parental education, and residential postal code (used as a proxy measure of household income).

#### Self-reported physical activity

The International Physical Activity Questionnaire – Short Form (IPAQ-SF) will be used to measure PA [40, 41]. Specifically, participants will be asked to respond to 3 items and indicate, during the last 7 days, on how many days they did 1) vigorous physical activities, 2) moderate physical activities, and 3) walked for at least 10 min at a time. If they indicate that they participated in an activity for one or more days, then they will be asked to indicate how much time (hours and/or minutes) they usually spent on one of those days participating in that activity.

#### Physical activity cognitions

The physical activity cognitions measures included are largely based on the M-PAC model [35]. Below are the specific measures included:

*Affective and Instrumental Attitudes* will be measured using 6 items and presented on a 7-point bipolar scale [42]. Each item will be prefaced with the stem “*Over the next 4 weeks, being physically active, for me, will be*”. The affective component will be captured by three items: unpleasant-pleasant, boring-fun and unenjoyable-enjoyable. The instrumental component will be captured by the three items: harmful-beneficial, bad-good and useless-useful.

*Behavioural Intention* for engaging in PA will be measured using a single item measure commonly used in the PA domain [43]. Participants will be asked to rate the extent to which the following statement is likely: “*I intend to do at least 150 minutes per week of moderate-to-vigorous physical activity*”. Response options will range from 1 (*extremely unlikely) to* 7 (*extremely likely)*.

*Task and Barrier self-efficacy* will be measured by adhering to recommendations from Bandura (2006) for assessing self-efficacy [44]. That is, each item will be prefaced with the stem “*How confident are you in your ability to* …” with responses ranging from 0 (*Not Confident*) to 10 (*Completely Confident*). For task self-efficacy, participants will be asked to rate their confidence to perform 7 items relating to physical activity behaviour such as *“to engage in PA*”, “*to engage in sports*”, “*to jump, hop, and skip*” and “*to balance*”. For barrier self-efficacy, participants will be asked to rate their confidence in being physically active if “*the weather was very bad*”, their “*schedule conflicted with [their] activity session*” and “*even if [they] felt overwhelmed with things to do*”.

*Perceived Opportunity* and *Perceived Capability* for engaging in physical activity will be measured by asking participants to indicate their agreement with 6 items pertaining to their perceived opportunity and perceived capability (i.e., confidence and/or control) for engaging in regular physical activity [45]. Each item will be rated on a 7-point *adjectival* scale ranging from 1 (*Strongly Disagree*) and 7 (*Strongly Agree*). Perceived opportunity items include “*If I really wanted to do regular physical activity over the next 4 weeks, I would have a chance to do so”*, *“I lack the opportunity to do regular physical activity over the next 4 weeks, even if I were really motivated to do so”*, and *“There are places where I can do physical activity around me if I had to*”. Perceived capability items include *“I possess the skills to do regular physical activity over the next 4 weeks if I wanted to”*, “*I have the physical ability to do regular physical activity over the next 4 weeks if I wanted to*”, and “*I am confident that I am capable of engaging in regular physical activity if I had to*”.

*Action Planning will be measured using the Behavioral Regulation for Physical Activity scale* [46] *which consists of 6 items that are rated on a 5-point Likert scale ranging from 1 (Strongly Disagree) to 5 (Strongly Agree). Example items include “I kept track of my physical activity over the last month”, “I set short-term (daily or weekly) goals for leisure-time physical activity last month” and “I made regular plans concerning ‘when’, ‘where’, ‘how’, and ‘what’ kind of physical activity I did last month”.*

*Social Support:* A modified version of the Multidimensional Scale of Perceived Social Support (MSPSS) will be used to assess social support [47]. Specifically, the 12-item measure includes three subscales, addressing a different source of support by either (a) family, (b) friends, and (c) significant others. Participants will be asked to what extent they agree with statements such as “*I get the emotional help and support I need from my family*”, “*My friends really try and help me*”, and “*There is a special person in my life whom I can share my happiness and sadness*”. Responses will be measured on a 7-point *adjectival* scale ranging from 1 (*Strongly Disagree*) to 7 (*Strongly Agree*). Previous research has demonstrated that the MSPSS has good internal and test-retest reliability as well as good construct validity [48].

*PA Identity* will be measured using the Exercise Identity scale [49], which asks participants how exercise is related to their concept of self. The Exercise Identity scale contains 5 items that are rated on a 7-point *adjectival* scale ranging from 1 (Strongly Disagree) to 7 (Strongly Agree). Participants will rate their agreement with statements such as “I consider myself as someone who is physically active” and “I would feel at a real loss if I were forced to give up physical activity”.

Self-Reported Habit for engaging in PA will be measured by the Self-Report Habit Index [50], asking participants about the extent to which engaging in physical activity is a habit for them. The Self-Report Habit Index contains 4 items that are rated on a 7-point Likert scale ranging from 1 (Strongly Disagree) to 7 (Strongly Agree). Each item will be prefaced with the stem “Regular physical activity is something …” . Example items include “… I do automatically” and “… I start doing before I realize I’m doing it”.

#### Psychosocial measures

*Trait Self-Control* will be measured using 5 items from the brief version of the Trait Self-Control Scale [51]. Each item will be rated on a 5-point *adjectival* scale ranging from 1 (*Not at all like me*) to 5 (*Very much like me*). The specific items include “*I have a hard time breaking bad habits*”, “*I am lazy*”, “*Fun sometimes keeps me from getting work done*”, “*I am able to work effectively toward long-term goals*”, *“I often act without thinking through all the alternatives*”, and “*I am good at resisting temptation*”.

*Fatigue* will be measured using the Chalder Fatigue Scale [52] which consists of 11 items that are rated on a 4-point *adjectival* scale ranging from 1 (*Less than usual*) to 4 (*Much more than usual*). Example items include “*Do you have problems with tiredness?*” and “*Do you have difficulties concentrating?*”

*Flourishing* will be measured using the Flourishing Scale [53] consisting of 8 items that are rated on a 7-point Likert scale ranging from 1 (*Strongly Disagree*) to 7 (*Strongly Agree*). Example items include “*I lead a purposeful and meaningful life*”, “*My social relationships are supportive and rewarding*”, and “*I am optimistic about my future*”.

*Self-Esteem* will be measured using a modified version of the Rosenberg Self-Esteem Scale [54] which measures global self-worth through statements relating to both positive and negative feelings relating to self. Included will be the 5 items that are associated with positive feelings towards self, “*On the whole, I am satisfied with myself*”, “*I feel that I have a number of good qualities*”, “*I am able to do things as well as most other people*”, “*I feel that I’m a person of worth, at least on an equal plane with others*”, and “*I take a positive attitude towards myself*”. Reponses will be rated on a 4-point *adjectival* scale ranging from 1 (*Strongly Disagree*) to 4 (*Strongly Agree*).

*Coping Resiliency* will be measured using 2-items that are rated on a 5-point scale ranging from 1 (*Poor*) to 5 (*Excellent*). Each item will be prefaced with the stem “*In general, how would you rate*”, and specific items include “*Your ability to handle unexpected and difficult problems (a family or performance crisis)*” and “*Your ability to handle day-to-day demands in your life (work, family responsibilities*)”. These items are consistent with those used in the Canadian Campus Wellbeing Survey [55].

*Sense of Belonging* will be measured using 3 items from the Sense of Belonging scale [56] rated on a 4-point *adjectival* scale ranging from 1 (*Strongly* Disagree) to 4 (*Strongly* Agree). The original scale is a 10-item measure that contains items relating to the domains of commitment, engagement and connectedness. The questions adapted for this study includes the three items from the engagement domain. Each item will be prefaced with the stem “*Thinking about your school, how much would you agree or disagree with the statements below*”, and the specific items include “*I feel comfortable at my school*”, “*I feel like I am part of my school*”, and “*I am supported at my school*”.

#### Ecological momentary assessment measures

Participants in Study II will be required to complete a series of 5 EMA prompts each day over the 7-day study period. Given the intensive sampling strategy, very brief questionnaires were developed to reduce participant burden (i.e., surveys designed to take one-to-two minutes to complete). The EMA questions will assess self-reported contextual information on current activity, current affective and feeling states, and measures of acute psychological processes consistent with M-PAC.

*Context-Specific Measures:* Each prompt sent to participants will include questions to obtain contextual information on three domains: (a) what participants are currently doing, (b) where participants currently are, and (c) with whom they are currently accompanied by. These items have been used in previous research, and have been found to be valid measures [57, 58].

*Affective and Feeling State* will be measured using the Hardy and Rejeski Feeling Scale [59]. Assessed on an 11-point scale, the 2 items ask “How do you feel right now” assessing acute arousal (− 5 Tired to + 5 Energetic) and valence (− 5 Very Bad to + 5 Very Good).

Reflective Process will be assessed using 2 items. First a single item of task motivation asking “How motivated are you to do physical activity right now?”. Responses will range from 0 (*Not motivated at all*) to 10 (*Extremely motivated*). Second, we will include a question of whether or not participants intend to do 10+ minutes of PA sometime within the next few hours (*yes/no*).

*Regulatory Process* will be assessed using 3 items*.* Two action control based questions will ask: “Could you do 10+ minutes of PA in the next hour even if you get busy?” and “Could you do 10+ minutes of PA sometime within the next few hours even if you get tired?”. Participants will respond on a 5-point scale from 1 (*I know I cannot*) to 5(*I know I can*). An additional item of self-control will also be included, asking: “If I were tempted by something right now, it would be very difficult to resist”. This item will be measured on 7-point scale ranging from 1 (*Not true)* to 7 *(Very true).*

*Reflexive Process* will be assed using a single item to capture habit-like behaviours. The question asks “Currently, I am doing something I would normally be doing on a typical day at this time”, with responses on a 5-point Likert scale from 1 (*Strongly disagree*) to 5 (*Strongly agree*).

#### Accelerometer-based physical activity

Participants in Study II will be asked to wear an ActiGraph GT9X Link on their non-dominant wrist for 7 complete days. This device will be set to collect data in 3 axes at a sampling rate of 30 Hz. Participants will be instructed to wear the device as much as possible while awake and sleeping, removing it only for prolonged water exposure. Wear time will be determined using the Troiano (2007) criteria, with any period ≥60 min of consecutive 0 counts flagged as non-wear [60]. Days that the accelerometer was dropped off and picked up will be excluded from analyses. PA data will only be analyzed for participants who meet the minimum wear time criteria (≥10 h on ≥3 days). Data will be analyzed using ActiGraph’s CentrePoint for daily total activity counts, average activity counts per minute, and daily steps.

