### Data analysis

For Study I, Structural equation modeling (SEM) and mixed effects modeling (MEM) will be used to address the primary research objectives of the current study. SEM will be used to test the M-PAC framework, modeling and identifying key influences related to PA pre-transition, and to examine the changes in latent (i.e. unobserved constructs) and observed variables through the transition into emerging adulthood. MEM or growth curve modeling will be used to examine the influences of individual factors on PA behaviours accounting for individual students nested within their classrooms and nested within schools. Our models will include indicators of SES and social cognitive factors (i.e., mediators), being entered as time-varying independent variables, while other socio-demographic factors (moderators) will be entered in our models as time-invariant independent variables.

For Study II we will use *time-varying effects modeling* (TVEM) to investigate the associations between momentary cognitions and subsequent PA [61]. TVEM models examine changes in the associations between intensively sampled environmental-contextual or momentary social cognitive factors as it relates to PA behaviours over time. This method can accommodate the unequal spacing of observations and unequal assessments across participants, typical of studies using EMA. Modeling time effects with intensive longitudinal data captures complex patterns of variation, and generally produces confidence regions rather than the *p*-values associated with hypothesis testing.

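### The accelerometer is worn day and night, but neither the 10-hour wear criterion nor counts per minute is limited to waking time, so sleep can qualify a day and dilute counts per minute

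*Protocol article*

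**What the plan says.** The Accelerometer-based physical activity section of the protocol article asks Study II participants to "wear an ActiGraph GT9X Link on their non-dominant wrist for 7 complete days". They are told to "wear the device as much as possible while awake and sleeping, removing it only for prolonged water exposure". The STUDY II recruitment section is consistent with this: students are asked "to wear it for as much as they can over the next week", with exceptions only for showering and water activities.

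The same measurement section then fixes three processing rules:

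- **Non-wear:** "any period ≥60 min of consecutive 0 counts flagged as non-wear".
- **Inclusion:** "PA data will only be analyzed for participants who meet the minimum wear time criteria (≥10 h on ≥3 days".
- **Outcomes:** "daily total activity counts, average activity counts per minute, and daily steps".

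No section gives a sleep-scoring step, a sleep log, a waking window or a waking-hours qualifier. The Data analysis section uses time-varying effects modelling (TVEM) in Study II "to investigate the associations between momentary cognitions and subsequent PA". Both studies have a baseline and three annual follow-ups.

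**The concern.** A 10 h threshold screens out days with too little observed activity only if the hours are waking hours. With round-the-clock wear, a night's sleep can supply most of them, so a day can qualify with very little waking activity observed.

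The zero-count rule does not repair this. It removes sleep only where the wrist is still enough to give an unbroken hour of zeros. Restless sleep stays in as wear and very quiet sleep drops out, so the amount of sleep counted varies between people and nights for reasons unrelated to physical activity.

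This matters because the Background names the scarcity of accelerometer-based follow-up as a gap, and the device is used again at each wave. Night-wear habits and sleep could plausibly change when participants leave school. A change of that kind would shift daily counts per minute even if waking activity stayed the same.

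**Working it through.** The article gives no figure on this point to reproduce, so the check is simple arithmetic on its rules.

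**Inputs from the article:** wear awake and asleep; non-wear at 60 min or more of consecutive zeros; at least 10 h on at least 3 days; average counts per minute as an outcome.

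**Assumptions, not in the article:** sleep of 7 to 9 h, central value 8 h; sleep counts per minute as a share *r* of waking counts per minute, 0 to 0.10, central value 0.05.

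**Step 1. Waking wear needed to reach 10 h.** Formula: max(0, 10 − *S*), where *S* is the hours of sleep counted as wear.

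| Sleep counted as wear | Waking hours needed |
|---|---|
| 0 h | 10 |
| 7 h | 3 |
| 8 h | 2 |
| 9 h | 1 |

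At 8 h, three qualifying days could hold as little as 3 × 2 = 6 waking hours. Under a waking-wear rule the minimum would be 3 × 10 = 30.

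**Step 2. Counts per minute relative to the waking value.** Formula: (*W* + *S* × *r*) / (*W* + *S*), where *W* is waking wear in hours. With *W* = 16, *S* = 8 and *r* = 0.05, this is (16 + 0.4) / 24 = 0.68, a fall of 32%. Over the assumed ranges with 24 h wear and no sleep flagged, the result runs from (17 + 0.7) / 24 = 0.74 (7 h, *r* = 0.10) to 15 / 24 = 0.625 (9 h, *r* = 0). That is a fall of 26% to 38%.

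**Step 3. Effect of the zero-count rule.** Keep *W* = 16, 8 h of sleep and *r* = 0.05, and let the rule remove a share of the sleep:

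| Share of sleep flagged as non-wear | Sleep left, *S* | Relative counts per minute |
|---|---|---|
| 0% | 8 h | 16.4 / 24 = 0.68 |
| 25% | 6 h | 16.3 / 22 = 0.74 |
| 50% | 4 h | 16.2 / 20 = 0.81 |
| 75% | 2 h | 16.1 / 18 = 0.89 |
| 100%, or device off at night | 0 h | 16 / 16 = 1.00 |

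The same waking activity therefore gives values from 1.00 down to 0.68.

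**Step 4. Totals and steps.** Sleep adds little to a daily total: under the central assumptions, 16.4 units with night wear against 16.0 without, or 2.5%. What lowers a total is missing waking wear. A day that qualifies on 8 h asleep and 2 h awake captures 2 / 16 = 12.5% of the waking total, if activity is spread evenly over the waking day.

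**The case against.** The best defence is that a journal article condenses its protocol. Sleep scoring, day windows and denominators are processing details that a fuller document could hold. The text also does not say outright that sleep counts toward the 10 h, or which minutes form the denominator. This stands only in part. The article does fix the wear instruction, the non-wear rule, the hour threshold and the outcomes, and applied together as written they let sleep in. A later sleep step would change how those rules operate.

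Other objections stand and limit the point:

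- **Totals.** A reader might infer that daily totals could differ 2.4-fold through wear time alone, from 24 h against 10 h. That needs equal intensity asleep and awake, which contradicts the low sleep counts assumed for the dilution. Sleep dilutes counts per minute only.
- **Typical size.** A reader might infer that people who remove the device at night will generally look 46% more active (1 / 0.683 = 1.46). That is the extreme contrast: no sleep flagged in one person and no night wear in the other. Everyone is instructed to wear the device at night, so among those who comply much of the dilution may be shared. A day of 8 h asleep and 2 h awake, with relative counts per minute of (2 + 0.4) / 10 = 0.24, is likewise possible under the rule, but nothing in the article shows how common it would be.
- **Study conclusions.** A reader might infer that the Study II results are biased. The only analysis stated for Study II is TVEM, which may use short windows after waking prompts, where dilution would matter less. The article specifies no between-wave model of daily counts per minute, and the self-reported activity measure is unaffected.

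**Conclusion.** The point holds in limited form. The stated wear, non-wear and inclusion rules do not separate sleep from waking, so any sleep not flagged as non-wear counts toward the 10 h and enters the counts-per-minute denominator. With 8 h of sleep all counted as wear, a day qualifies on 2 waking hours. With sleep at 5% of waking counts, counts per minute fall 0 to 32% below the waking value. Where a person falls in that range depends on night wear and on how much sleep the zero-count rule happens to remove. Daily totals and steps are not diluted, but they are understated on days that qualify mainly through sleep.

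The mechanism follows from the text. The size rests on the assumed sleep length and count ratio, and the frequency of affected days is unknown. An effect on estimated change across the transition is plausible, but the article does not establish it.

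**What to change.** Amend the accelerometer section, with identical rules at every wave:

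1. Identify sleep in the recorded files, or apply one common waking window to all participants.
2. Define the 10 h as waking wear.
3. Compute average counts per minute over waking wear only.
4. Adjust daily total counts and steps for waking-wear minutes.

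Each qualifying day would then hold at least 10 waking hours, and sleep correctly identified would no longer dilute counts per minute. If a 24 h measure is intended, the alternative is to state an explicit 24 h wear criterion and a 24 h outcome.

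The change uses data already being recorded and leaves the wear instruction as it is. It costs one more processing step and the loss of days that qualify only through sleep, and some participants may then fall below three qualifying days.
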